## Abstract

**Introduction/Aim:** As the prevalence of atrial fibrillation (AF) increases with the aging population, the challenge of enhancing the detection rate of AF in embolic stroke of undetermined source (ESUS) has intensified. AF is often detected only after a debilitating or fatal cardioembolic stroke, underscoring the crucial need for early identification to prevent further ischemic stroke (IS). This study aims to assess the efficacy of AF detection in patients with ESUS using a single-lead patch (mobiCARE™; Seers Tech, Inc.) over a period of at least 72 h and up to 5 days, in comparison with standard 24 h Holter monitoring. **Design:** This multicenter, prospective, consecutive observational trial involves patients aged 18 years and older who have experienced an IS within the past six months. **Study outcomes**: The primary outcome is the initial detection of AF using either a single-lead wearable patch or 24 h Holter monitoring at both baseline and at a 6-month follow-up among patients diagnosed with ESUS stroke. Secondary outcomes include the first detection of AF among stroke patients with large-artery atherosclerosis or small-vessel occlusion, particularly those whose transthoracic echocardiography reveals a left atrial size of ≥44 mm, an echocardiographic marker of AF. **Discussion:** Prolonged cardiac monitoring increases the detection rate of paroxysmal AF, but the optimal method should be non-invasive, patient-friendly, and accurate. This new technology may reduce patient burden and socioeconomic impact by facilitating AF detection and preventing cardioembolic stroke, even in patients with non-cardiogenic stroke.

## 1. Introduction

The growing prevalence of atrial fibrillation (AF) coincides with the global increase in the elderly population and ranges from 0.4% to 2% among adults [1]. AF, a common arrhythmia, often becomes apparent only after a severe or fatal cardioembolic event. Conventional Holter monitoring, particularly in cases without a clearly identified high-risk cardioembolic source, demonstrates low AF detection rates. Moreover, in patients with traditional atherogenic stroke, recurrent stroke is often associated with AF-related pathologies [2]. Therefore, the early detection of AF is critical for the effective prevention of recurrent events.

In approximately one-third of ischemic stroke (IS) cases, there is no immediately identifiable embolic cause, leading to classification as an “embolic stroke of undetermined source” (ESUS). Notably, over 30% of ESUS patients are found to have underlying paroxysmal atrial fibrillation (pAF) [3]. However, the rate of AF detection via short-term ECG monitoring in these patients is only about 2–3%, suggesting that AF frequently remains undetected. Long-term monitoring using implantable loop recorders (ILRs) achieves detection rates of approximately 23–30%. Although the 2023 European Stroke Organization (ESO) guidelines recommend more than 48 h of continuous cardiac monitoring with an ILR for AF screening in all patients with IS and ESUS [4], its invasive nature limits widespread use [5]. Consequently, echocardiographic indicators such as left atrial (LA) enlargement and laboratory markers like NT-proBNP are used as supplementary tools for AF detection.

The 2020 guidelines from the European Society of Cardiology recommend the use of wearable devices for single-lead ECG recording, with a Class Ia recommendation for AF diagnosis confirmation [6]. Furthermore, a comprehensive systematic review and meta-analysis, which included 47 studies, supports a non-invasive rhythm monitoring strategy as an initial approach before adopting invasive techniques [7]. Based on these findings, a non-invasive single-lead wearable monitoring device may be more sensitive and effective for AF diagnosis than traditional Holter monitoring, thereby reducing the need for repeated ECG tests.

This study aims to evaluate the efficacy of AF detection using a single-lead patch compared to conventional 24 h Holter monitoring in stroke patients identified with ESUS. Additionally, we aim to explore the detection rates of incidental AF in patients exhibiting LA enlargement or elevated NT-proBNP levels, providing potential indicators of AF in patients with non-cardioembolic stroke, including those due to large-artery atherosclerosis (LAA) and small-vessel occlusion (SVO).

## 2. Design

### 2.1. Trial Design

The AVANT-GARDE trial, a multicenter, prospective, observational trial (registration number cris.nih.go.kr KCT0008110), is designed to detect AF in patients with IS using the single-lead wearable patch and comparing it with 24 h Holter monitoring.

### 2.2. Rationale for Investigation

Earlier studies investigating the effectiveness of non–vitamin K-dependent oral anticoagulants (NOACs) and aspirin in ESUS patients revealed ambiguities regarding eligibility criteria, potentially including patients with atherothrombotic origins, thereby leading to inconclusive outcomes [8,9,10]. To improve the precision and specificity of the inclusion criteria related to cardioembolic mechanisms, we incorporated additional diagnostic evaluations such as brain imaging markers (embolic imaging patterns), transthoracic echocardiographic (TTE) indicators (LA size and E/e′ ratio), and serum markers (NT-proBNP) [11].

### 2.3. Definition of ESUS

ESUS is defined as an embolic stroke that is non-lacunar (with a lesion size greater than 1.5 cm on CT or greater than 2 cm on magnetic resonance imaging [MRI]) and non-atherosclerotic, without proximal arterial stenosis (>50%) in the culprit artery or known high-risk cardioembolic sources [12]. Embolic imaging patterns include multiple infarcts, simultaneous involvement of different circulations, and isolated cortical infarcts [13].

### 2.4. Study Population

Nine hospitals in South Korea participated in this trial: Eunpyeong St. Mary’s Hospital, the Catholic University of Korea, Kangdong Sacred Heart Hospital, Gachon University Gil Medical Center, Hanyang University Myongji Hospital, SMG–SNU Boramae Medical Center, Soon Chun Hyang University Hospital Bucheon, Inje University Sanggye Paik Hospital, and Chosun University Hospital. Each institution is equipped with a dedicated stroke unit and the necessary monitoring and imaging facilities to provide standardized stroke care by experienced specialists.

The absence of diagnosed AF at admission, confirmed through baseline surface ECG, is the key criterion. Eligible participants are as follows: (1) age over 18 years, (2) non-lacunar infarction or non-atherosclerotic cerebral infarction without corresponding artery stenosis > 50% (less than 6 months after stroke onset), (3) no history of AF and showing no AF during initial monitoring, (4) at least 18 h of recording on 24 h Holter monitoring, (5) at least 72 h of recording on a single-lead wearable patch, and (6) who underwent MRI and TTE examination. Subjects were excluded if they (1) exhibited AF on baseline ECG, (2) had valvular heart diseases (e.g., rheumatic mitral stenosis, a mechanical or bioprosthetic heart valve, or mitral valve repair, infective endocarditis), (3) had underlying disease related to AF (recent cardiothoracic and noncardiac surgery (<2 weeks), recent ST-elevation myocardial infarction (MI) (<3 months), pericarditis, myocarditis, hyperthyroidism, electrocution, pneumonia, and pulmonary embolism), (4) had implanted pacemakers, (5) suffered from advanced systemic disease or coexisting neurological/psychiatric conditions, (6) had contact dermatitis or other skin disorders, (7) lacked data on transesophageal echocardiography, or (8) were unable to participate in the study due to other causes.

According to the TOAST classification system, large artery atherosclerosis is defined as corresponding artery stenosis > 50% and small-vessel disease as a subcortical lesion < 15 mm. Patients whose index stroke was LAA or SAO were included if they exhibited LA enlargement.

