### 2.7. Concomitant Application

At baseline, upon enrollment, AF detection rates are concurrently compared using a single-lead wearable patch and a 24 h Holter monitor, with observations spanning 48 h. The Holter monitor is used for 24 h (at least 18 h), whereas the single-lead wearable patch is applied for 5 days (at least 72 h). Patients with ESUS will undergo follow-up assessments using both the single-lead patch and the 24 h Holter monitor at enrollment (visit 0) and at 6 months (visit 1).

In the context of clinical AF, this study follows a specific definition: AF is identified when an ECG recording captures an episode lasting 30 s or longer. This definition aligns with the criteria established in the 2020 European Society of Cardiology guidelines for the diagnosis and management of AF [6].

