### 2.9. Sample-Size Estimates

The sample-size calculation is based on the primary endpoint: “the detection probability for each group.” The detection probabilities were estimated as follows: standard treatment at 2.8% and automated continuous ECG monitoring at 15.8%, based on prior studies [20]. To establish the non-inferiority of the single-lead patch monitor with a significance level (alpha) of 5% and a power (1-beta) of 80%; each group requires 55 patients, considering a 20% drop-out rate. The calculation was performed using the Power and Sample Size website (http://powerandsamplesize.com/Calculators/Compare-2-Proportions/2-Sample-Non-Inferiority-or-Superiority, accessed on 22 November 2021). Given that this study adopts an intention-to-treat approach, our intended analysis includes cases of participant drop-out, excluding situations where a subject actively requests data removal. The first enrollment of the AVANT-GARDE commenced in April 2023, and the recruitment ended in 2024 with 116 participants.

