### Study Limitations

This study has several limitations. First, it is not a randomized controlled trial, but rather a non-blinded, prospective observational study; therefore, the possibility of detection bias cannot be excluded. Second, the accuracy and completeness of measurements largely depend on patient cooperation. Third, the relatively short follow-up period of six months may underestimate the rates of AF diagnosis and recurrent stroke incidence. Fourth, patients with ESUS will undergo follow-up evaluations at enrollment (visit 0) and at 6 months (visit 1). The 6-month interval may be too long, potentially resulting in missed episodes of paroxysmal AF (pAF). However, a recent meta-analysis of randomized controlled trials (RCTs) conducted between 2012 and 2023 investigating new AF detection after ischemic stroke (IS), and transient ischemic attack (TIA) identified two statistically significant time windows for new AF detection: 0–14 days and 6–12 months [26].

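### Minimum recording times on the two study devices are inclusion criteria, so the baseline comparison is completers-only and conflicts with the stated intention-to-treat analysis

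*Protocol article*

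**What the plan says.** Section 2.4 (Study Population) gives as inclusion items "4) at least 18 h of recording on 24 h Holter monitoring, (5) at least 72 h of recording on a single-lead wearable patch". The item before these reads "3) no history of AF and showing no AF during initial monitoring"; it does not define the initial monitoring.

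Section 2.7 (Concomitant Application) places the recordings at entry: "At baseline, upon enrollment, AF detection rates are concurrently compared using a single-lead wearable patch and a 24 h Holter monitor". It repeats the two minimums beside the planned wear of 24 h for the Holter and 5 days for the patch.

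Section 2.9 (Sample-Size Estimates) describes the analysis population: "Given that this study adopts an intention-to-treat approach, our intended analysis includes cases of participant drop-out". The one exception is "excluding situations where a subject actively requests data removal". The same section allows for 20% drop-out and assumes "standard treatment at 2.8% and automated continuous ECG monitoring at 15.8%, based on prior studies".

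Study Limitations concedes that "the accuracy and completeness of measurements largely depend on patient cooperation".

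**The concern.** Eligibility should rest on what is known before the tests under comparison are used. Hours recorded are a result of wearing the device. If reaching the minimum is an entry condition, a patient whose baseline patch came off before 72 h, or whose Holter gave less than 18 h, is removed from the denominator instead of being counted as someone in whom the device gave a limited result.

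Two things are at stake. First, the analysis set is ambiguous: Sections 2.4 and 2.9 give opposite answers for the same patient, so two analysts could build different primary populations. Second, the article presents the patch as an effective and patient-friendly method. A sample selected on successful wear shows what the patch finds when it works, not what it finds per patient fitted.

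**Working it through.** **Text, side by side.** Take an ESUS patient with 60 h of patch recording and 20 h of Holter recording at baseline.
- Section 2.4: fails item (5), so not eligible.
- Section 2.9: has not asked for data removal, so analysed.
- Section 2.7: both recordings start at enrolment, so the patient was already enrolled when the shortfall became known.

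The conflict concerns the baseline visit. A patient who meets both minimums at baseline and is lost before the 6-month visit can be kept under intention to treat without contradiction.

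**Inputs.** Patch yield p = 15.8% and Holter yield h = 2.8% (Section 2.9). The plan's own contrast is 15.8 − 2.8 = 13.0 points, with ratio 15.8/2.8 = 5.6. The stated 55 per group does not enter the calculation.

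**Assumptions, not in the documents.**
- p and h are the yields in complete recordings.
- f is the share of fitted patients below the patch minimum, varied from 5% to 30%; g is the same for the Holter.
- r is the share of the yield kept in a short recording, set to 0 or 0.5.
- Failing the minimum is unrelated to having AF.

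**Formulas.** Patch yield per fitted patient = p × [1 − f(1 − r)]. Holter yield per fitted patient = h × [1 − g(1 − r)].

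**Results with no Holter failure (g = 0).**

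| f | Patch yield, r = 0 | Difference, r = 0 | Patch yield, r = 0.5 | Difference, r = 0.5 |
|---|---|---|---|---|
| 5% | 15.0% | 12.2 | 15.4% | 12.6 |
| 10% | 14.2% | 11.4 | 15.0% | 12.2 |
| 20% | 12.6% | 9.8 | 14.2% | 11.4 |
| 30% | 11.1% | 8.3 | 13.4% | 10.6 |

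Example: f = 20%, r = 0 gives 15.8 × 0.80 = 12.6%, and 12.6 − 2.8 = 9.8 points.

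**Both devices failing.** With f = g = 20% and r = 0, the Holter yield is 2.8 × 0.80 = 2.2%. The difference is 10.4 points and the ratio stays at 5.6. With f = 10%, g = 20% and r = 0, the yields are 14.2% and 2.24%, so the ratio is 6.3 and the completers' 5.6 understates it. The completers' difference is too large whenever p × f > h × g, that is, unless g exceeds 15.8/2.8 = 5.6 times f.

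**Power.** Exact two-sided McNemar test at 5%, with a 20% loss and r = 0 on both devices, discordant probabilities written as (patch only, Holter only):
- All 55 pairs, losses scored negative: 51.5% at (0.104, 0) and 40.5% at (0.123, 0.019).
- Completers only, 55 × 0.8 = 44 pairs at the unreduced rates: 51.7% at (0.13, 0) and 40.7% at (0.1536, 0.0236).

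The two sets are practically equal, so the filter has no material effect on power.

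**The case against.** Several counter-arguments have force.

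- **A baseline evaluability filter can coexist with intention to treat for later losses.** This stands for the 6-month visit, and the 20% drop-out allowance makes sense on that reading. It does not rescue the baseline visit, because Section 2.9 makes no exception for short recordings.
- **The loss may not go against the patch.** A reader might infer that the longer wear makes the patch fail more often. The documents do not support that: both devices are filtered, Section 2.6 names the Holter as the device with reduced compliance, and the minimum is 60% of planned wear for the patch (72 of 120 h) against 75% for the Holter (18 of 24 h). The comparative ratio may be inflated, unchanged or deflated.
- **The size is unknown.** The 20% in Section 2.9 is overall drop-out, not a rate of wear below 72 h, and cannot be read as a device-failure rate. Short recordings can contain AF, and the primary outcome also draws on the 6-month visit. If patients with AF failed the minimum more often than others, the filter could even lower the observed yield; nothing in the documents describes that.
- **Criterion (3).** A reader might infer that patients with AF on the baseline study devices are ineligible, which would remove primary-outcome events. Section 2.4 calls absence of AF on the baseline surface ECG the key criterion, and initial monitoring can naturally be read as the work-up before the study. This needs clarifying; it is not a demonstrated fault.
- **An article condenses, and scoring rules are often left to an analysis plan.** This is fair for the scoring rule. The eligibility items, however, are stated outright and conflict with another stated rule.

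**Conclusion.** The point holds in a limited form. Section 2.4 makes entry depend on the success of the tests being compared, contradicts the intention-to-treat statement for baseline failures, and turns the baseline comparison into one of completers.

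The direction is clear for the patch's own yield, provided that short recordings find less AF than complete ones and that failing the minimum is unrelated to AF. Under the same conditions the risk difference is also overstated, unless Holter failures are more than about 5.6 times as frequent as patch failures. For an assumed patch shortfall of 5–30%, the overstatement of the yield is between 15.8 − 15.4 = 0.4 and 15.8 − 11.1 = 4.7 points. The documents cannot narrow that range.

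Two stronger conclusions are not supported. Low power at 55 pairs is not caused by this filter. And nothing shows that any patient was in fact left out for a short recording.

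**What to change.** - Remove items (4) and (5) from eligibility.
- Define the primary set as all consented ESUS patients fitted with both devices at baseline.
- Score both devices by the same rule: AF of 30 s or longer anywhere in the recorded time counts as detected; a short or absent recording without AF counts as not detected.
- Keep the set with at least 18 h of Holter and at least 72 h of patch recording as a per-protocol sensitivity analysis.
- Report how many patients, if any, were left out for short recording on each device, and include them where their recordings exist.
- State in item (3) that initial monitoring means monitoring before the baseline study devices are applied.

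Recruitment has ended, so the cost is wording, a count of affected patients and retrieval of any recordings that were kept. The patch detection rate may come out somewhat lower.

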### 2.5. Transthoracic Echocardiography

Transthoracic echocardiography (TTE) provides comprehensive information on cardiac chamber size (particularly left atrial size), wall thickness, and geometry, as well as quantitative measurements of ventricular systolic and diastolic function. It can also identify regional wall motion abnormalities that are suggestive of myocardial ischemia, and assess global ventricular performance using parameters such as ejection fraction and strain analysis. In addition, TTE enables the evaluation of cardiac valves in terms of morphology, motion, and hemodynamic function, allowing for the determination of stenosis or regurgitation severity.

Recent studies have indicated that left atrial enlargement may predispose individuals to AF [14,15]. Seko et al. demonstrated that left atrial enlargement (>40 mm) and reduced left ventricular ejection fraction (LVEF < 50%) were the strongest parameters associated with AF, surpassing left ventricular geometry [14]. In a previous study involving patients with isolated mitral valve disease, a significant correlation was identified between LA size and the occurrence of AF. AF was rare when the left atrial dimension was below 44 mm (3%), but prevalent when exceeding 40 mm (54%), highlighting the potential clinical utility of left atrial size in decisions regarding prophylactic anticoagulation and elective cardioversion [16].

Current Doppler echocardiography guidelines recommend assessing diastolic function by considering the ratio of early-to-late diastolic transmitral flow velocities (E/A) and by using the ratio of early diastolic mitral inflow velocity to early diastolic mitral annular tissue velocity (E/e′) as an indicator for estimating left ventricular filling pressures [17]. In patients with ESUS who underwent insertable cardiac monitoring, a high E/e′ ratio (≥8.65) was independently associated with AF detection after adjustment for age and sex [18].

### 2.6. Single-Lead Wearable Patch

An innovative, adhesive single-lead ECG patch (mobiCARE-MC100™; Seers Technology, Seongnam-si, Gyeonggi-do, Republic of Korea) weighing only 9.2 g and requiring no supplementary components has been developed for the identification of arrhythmias. This device enables uninterrupted, continuous ECG monitoring and offers greater comfort compared to conventional Holter monitors. The 24 h Holter monitoring device is relatively bulky, less comfortable for patients, and may interfere with daily activities, leading to reduced compliance.

Users can review their ECG recordings via a mobile phone application, and data are transmitted seamlessly to a central laboratory. Utilizing an artificial intelligence–driven algorithm, this single-lead ECG patch robustly classifies and analyzes data, thereby enhancing diagnostic accuracy. Notably, the device’s superior signal fidelity—stemming from its effective mitigation of motion artifacts—significantly aids in the precise detection of heartbeats [19]. ECG data are transmitted through a secure server managed by the device manufacturer. Clinicians interpreting both Holter and patch ECGs are blinded to clinical information.

Cardiac rhythm and heart rate variability data were obtained using the single-lead wearable patch (mobiCARE-MC100™). Continuous electrocardiographic monitoring with this device allowed for the detection of arrhythmias, including atrial fibrillation, premature atrial and ventricular contractions, and pauses. Average heart rate, heart rate trends, and episodes of tachycardia or bradycardia were also recorded and analyzed.

These data are accessible only to authorized personnel responsible for patient care or individuals granted approval by the Institutional Review Board (IRB) for the study’s intended use. Importantly, the device manufacturer did not participate in the trial design, data collection, or analysis.

### 2.7. Concomitant Application

At baseline, upon enrollment, AF detection rates are concurrently compared using a single-lead wearable patch and a 24 h Holter monitor, with observations spanning 48 h. The Holter monitor is used for 24 h (at least 18 h), whereas the single-lead wearable patch is applied for 5 days (at least 72 h). Patients with ESUS will undergo follow-up assessments using both the single-lead patch and the 24 h Holter monitor at enrollment (visit 0) and at 6 months (visit 1).

In the context of clinical AF, this study follows a specific definition: AF is identified when an ECG recording captures an episode lasting 30 s or longer. This definition aligns with the criteria established in the 2020 European Society of Cardiology guidelines for the diagnosis and management of AF [6].

### 2.8. Clinical Monitoring

During the 6-month follow-up period, both AF detection rates and the occurrence of recurrent stroke will be evaluated. Recurrent stroke will be confirmed by brain MRI or CT imaging.

